### Data analysis

Data will be entered into a SPSS database and double-checked by student assistants blinded to the group allocation. Simple plausibility checks will be done in the study center before the final statistical analysis by the statistician. Analysis of all quantitative data will use the intention-to-treat principle. Missing values in primary and secondary outcomes will be imputed using simple methods. A dropout analysis comparing baseline parameters between the study population and early dropouts (before T2) will be performed.

All statistical tests are two-sided using a significance level of 5%. Baseline parameters are described by frequency tables, means, standard deviations or quartiles.

The primary outcome is the percentage of correct answers for the knowledge test at T1. Assuming approximate normal distribution, the expected values from the IG and CG will be compared with adjustment for stratified randomization by professionals and volunteers using bifactorial analysis of variance (linear model). Distribution assumptions will be investigated by graphical methods. Furthermore, interactions between intervention and professional status will be included in a secondary model. Different effects depending on the professional status will be discussed.

The secondary outcome of sufficient knowledge (binary) at T1 will be compared between IG and CG using bivariate logistic regression, including IG/CG and professional status as independent variables. Additionally interactions between intervention and professional status will be investigated in a second model.

The sustainability of knowledge will be investigated at T3. The time course of the knowledge between T1 and T3 will be analyzed by fitting a linear mixed model: the dependent variable is knowledge (% of correct answers), and the independent variables are IG/CG, time (T1, T3), interaction between intervention and time, professional status and interaction between intervention and professional status. To adjust for repeated measurements of the legal representatives, random effects are included (covariance pattern model with covariance structure compound symmetry).

Further secondary outcomes are the numbers of persons concerned and the percentage of these persons affected by PEG, FEM or AP (separately) per legal representative at T3. Mean values ± standard deviations will be described for IG and CG at T3 as well as at T0. Linear models will be fitted including IG/CG and initial values at T0 as independent variables.

Finally, the results of the first decision about PEG, FEM or AP by the legal representative after T0 (e.g., after training for IG, or after randomization for CG) will be assessed. Initially, the duration from T0 to the first decision will be described for IG and CG by Kaplan-Meier curves. In case of no decision, durations are censored at the end of observation after 6 months or at dropout. Kaplan-Meier curves between both groups will be compared by the log rank test, as long as there are no clear deviations from the proportional hazard assumption in the graphics. Four categories of decisions will be described by frequency tables.

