### Sample size

No information was available for the primary outcome from previous studies. The assessment instrument was pretested with a before-after design to roughly estimate the expected intervention effect in the primary outcome of knowledge (given as a percentage of correct answers). The knowledge test was revised after three courses with a total of 18 legal representatives. Afterwards, two pilot courses with 16 participants were used to estimate the effect size of the intervention. Fifteen datasets before intervention, and 12 after intervention, were included in the analysis.

A common standard deviation of σ = 0.17 can be assumed in IG and CG. A mean difference of 0.085 between IG and CG can be detected by a power of 90% by the two-sided t-test, using a significance level of 5% based on a sample size of 86 per group (172 overall). Including a maximum dropout rate of 20%, an overall sample size of 216 is planned. The pilot study estimated a larger effect (0.38). Because of the low sample size, and considering a possible bias in the pilot study, the planned sample size is higher than theoretically necessary. It corresponds to a medium effect of 0.5*σ, as suggested by Cohen.

With six to ten participants per training session, the education program will be offered approximately 24 times (12 times per group).

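### Imputing missing outcomes by unnamed simple methods leaves the primary test's type I error anywhere from about 5% to about 12% at the maximum planned dropout, depending on the method

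*Protocol article*

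**What the plan says.** All statements are in the protocol article.

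- Data analysis: "Analysis of all quantitative data will use the intention-to-treat principle". Next comes the rule at issue: "Missing values in primary and secondary outcomes will be imputed using simple methods". The section also plans a comparison of baseline parameters between early dropouts and the study population.
- Data analysis, primary outcome: the percentage of correct answers at T1, compared between arms by a linear model with arm and professional status, two-sided at 5%.
- Data analysis, sustainability: "The time course of the knowledge between T1 and T3 will be analyzed by fitting a linear mixed model".
- Data analysis, first decision: durations without a decision are censored at six months or at dropout.
- Sample size: both arms are taken to share an SD of 0.17, and a difference of 0.085 is to be found with 90% power from 86 evaluable participants in each arm. On losses, the section says: "Including a maximum dropout rate of 20%, an overall sample size of 216 is planned".
- Data collection and Table 1: knowledge is tested at T1 and T3 only. Single unanswered items count as wrong; a test with four or more of 13 items unanswered gets no score.

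**The concern.** The sentence is a positive commitment covering every primary and secondary outcome, so an analysis plan that follows it inherits the problem. Single imputation puts fixed values in place of unobserved scores, and the model then treats them as data. Depending on the method, this understates the standard error, pulls the effect towards zero or costs power.

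Three parts of the plan are exposed:

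- The primary test and its confidence interval, which could rest on up to 22 filled-in scores per arm.
- The T1–T3 mixed model. It can already use participants with only one of the two scores, validly under missing-at-random, and filling its data beforehand gives that up.
- Time to first decision. It is a secondary outcome, so the imputation sentence covers it, yet the same section censors it at dropout.

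**Working it through.** **Inputs.** SD 0.17, difference 0.085, 86 evaluable per arm, maximum dropout 20%, 216 randomised (Sample size); 1:1 allocation (Design); two-sided 5% and a linear model with arm and professional status (Data analysis).

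**The plan's own figure.** With a standardised difference of 0.085/0.17 = 0.5, the noncentral t gives 89.99% power at 85 per arm and 90.3% at 86. Then 86/0.80 = 107.5, rounded up to 108 per arm, or 216. The sample size reproduces, and it provides for dropout without any filled-in values.

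**Arm-mean filling.** Let N = 108 be randomised and r observed per arm. Filling with the arm mean adds nothing to the residual sum of squares, but the variance is divided by N − 1 instead of r − 1 and the mean is credited with N observations instead of r. So

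reported SE / true SE = √[(r − 1)/(N − 1) × r/N].

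At 20% missing, r = 86: √(85/107 × 86/108) = 0.795. The true SE is 0.17 × √(2/86) = 0.0259; the reported one is 0.795 × 0.0259 = 0.0206. Type I error is the probability that |t| on 2r − 2 degrees of freedom exceeds the nominal critical value times this ratio.

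| Missing per arm | r | SE ratio | Type I error |
|---|---|---|---|
| 5% | 103 | 0.954 | 6.2% |
| 10% | 97 | 0.898 | 7.8% |
| 15% | 92 | 0.851 | 9.5% |
| 17% | 90 | 0.833 | 10.3% |
| 20% | 86 | 0.795 | 11.9% |

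At 20% missing, a nominal 95% interval therefore covers about 100 − 11.9 = 88%.

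**Methods compared at 20% missing in both arms.** The planned two-factor model was simulated under no effect, with 20,000 runs per method and scores missing completely at random. Assumptions not in the documents: strata of equal size, a stratum difference of 0.05, and a control-arm mean of 0.45 in the lower stratum.

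| Method | Type I error | Other consequence |
|---|---|---|
| Observed cases only | 5.3% | power 90.3% at a difference of 0.085 |
| Overall mean | 5.0% | effect × 86/108 = 0.80, so 0.085 becomes 0.068 |
| Control mean | 5.1% | effect diluted by the same factor |
| Hot-deck within arm and stratum | 10.3% | – |
| Arm mean within stratum | 11.5% | – |
| Arm mean | 11.8% | agrees with the formula |
| Missing scored as zero | not inflated | power about 46% (depends on the assumed mean level) |

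With unequal dropout of 25% and 15%, the arm mean gives 11.9%, the hot-deck 10.6% and zero-scoring 21.6%; observed cases stay at 5.0%.

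**Carrying forward.** With no T0 knowledge score, nothing can be carried forward to T1. At T3 it is possible: if 20% of T3 scores were replaced by the same person's T1 score, with data missing completely at random, the mean change from T1 to T3 would be multiplied by 0.80, understating any decline by about 20%.

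**The case against.** The best defence is that this is a condensed article and that the choice among simple methods can be left to an analysis plan. That holds for the name of the method. It does not cover the commitment itself, which steers any analysis plan towards single imputation. None of the simple methods examined for T1 knowledge avoids both faults: each either understates the standard error or dilutes the effect or loses power.

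Other parts of the defence stand:

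- A reader might infer that the primary confidence interval and p-value will be too optimistic, or that type I error will more than double. The documents do not support that. Overall-mean or control-mean filling keeps the error near 5%, and for the arm mean doubling needs about 17% missing or more.
- A reader might take 172 as the number the plan expects to analyse. The 20% is stated as a maximum, so 172 is close to the floor. T1 falls at the end of training or within two weeks, and the protocol describes reminders and stamped envelopes, so T1 missingness may well be lower.
- The carry-forward criticism concerns T3 alone, and only if that method were chosen.
- Some secondary outcomes have their own handling: censoring for time to first decision, and PEG, restraint and medication status recorded when a person concerned leaves early.
- If the pilot difference of 0.38 held, the primary result would probably be significant under most methods. The protocol itself distrusts that figure and plans on 0.085.

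Against the defence, missing completely at random is a favourable assumption. Intervention participants may complete the test on the spot while controls receive it by mail, so unequal missingness is plausible.

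**Conclusion.** The concern holds in conditional form. The sentence commits the trial to a class of methods in which the choice alone moves the primary test's type I error from about 5%, with a diluted estimate, through about 10% to about 12% at the dropout ceiling. At 5% to 10% missing, arm-mean filling costs about 1 to 3 percentage points. These figures rest on reading simple methods as single imputation analysed as observed data, on missingness completely at random and on equal dropout. Inflation is possible, not established. The design and sample size are sound. This should be fixed before analysis, but it does not undermine the trial.

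**What to change.** Replace the imputation sentence with the following rules.

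1. **T1 knowledge and the binary T1 outcome:** multiple imputation by arm, using professional status, the T0 covariates (age, gender, education, time since appointment, number of persons concerned) and T3 knowledge, with results combined so that the uncertainty from missing data enters the standard error. Report the observed-case linear model alongside. Participants missing both T1 and T3 will gain little from imputation, so the two results should be close unless the covariates predict knowledge well.
2. **T1–T3 mixed model:** fit to observed scores, without prior imputation.
3. **Time to first decision:** keep censoring at dropout and exempt this outcome from imputation, so that the section no longer says two things.
4. **Sensitivity:** one simple missing-not-at-random analysis, for example shifting the imputed scores by a stated amount in one arm and then the other.

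The cost is slightly wider intervals than single imputation might report and a little more programming. No new data are needed, and 216 already allows for dropout: observed cases keep about 5% type I error and 90% power at 20% missing, if data are missing completely at random.

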### Randomization and blinding

After retrieval of written informed consent and baseline data, participants will be allocated to the intervention group or to the control group, stratified by professionals and volunteers (Fig. 1). To ensure a close balance of entities in each group, randomization will be performed by randomly selected block sizes of four and six. The randomization list will be computer generated by a scientist who is not involved in either the intervention or data collection. An independent person will also perform the allocation. As safeguards, no other person will have access to the list, and the list will be sent by e-mail only in an encrypted format.

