### Data collection

In the T0 baseline, data of legal representatives will be assessed according to age, gender, education status, activity status (professional or voluntary representative), time since appointment as legal representative and number of persons concerned. Additionally, baseline data and baseline outcome measurements of persons concerned will be assessed. For this, legal representatives will receive a pseudonymization list, documentation sheets and a standardized written introduction. A pseudonymization number will be assigned to each person concerned with dementia. All data will be given to the study site under this pseudonym. The legal representative, using data extracted from routine documentation, will fill in the documentation sheets. The age range, gender, diagnosis additional to dementia, presence of PEG, number and types of PR, name and dosage of antipsychotics will be assessed by multiple choice and free-response questions. Copies of the routine documentation (e.g., a list of drug prescriptions) will be passed on only if pseudonymization is safeguarded.

At T1, the primary outcome *knowledge* will be assessed (Table 1). To assess understanding and realistic expectations, a novel questionnaire was developed based on Bloom’s taxonomy [40], the *User Manual–Realistic Expectations* [41], the contents of the education program, and the evidence-based information for PEG, PR and AP in people with dementia. The questionnaire comprises 13 items: two items on the understanding of decision-making processes in healthcare affairs; two items on quality and validity of study results; and nine items on realistic expectations regarding probabilities of benefits and harms of PEG, PR and AP to people with dementia (with three items per intervention). All items are multiple choice questions with four choices, with only one correct answer. Questions with more than one answer and unanswered questions will count as a wrong answer. No summarizing score is given if four or more of the 13 questions remain unanswered.

**Table 1 Tab1:** Data collection

Outcomes	Measures	Follow-up
Knowledge	Questionnaire developed on the basis of evidence-based information and contents of the education program	T1, T3
First decision PEG	Standardised telephone interview	T2, T3
First decision PR	Standardised telephone interview	T2, T3
First decision AP	Standardised telephone interview	T2, T3
Physical restraints	Documentation sheet; medical and nursing records	T3

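### The primary model is valid and adequately powered, but adjusting also for education and age, already collected before allocation, is a near-free option to gain precision

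*Protocol article*

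**What the plan says.** Under Data analysis, the endpoint is fixed: "The primary outcome is the percentage of correct answers for the knowledge test at T1". The two arms are to be "compared with adjustment for stratified randomization by professionals and volunteers using bifactorial analysis of variance (linear model". The model therefore has two factors, arm and professional status. A secondary model adds their interaction.

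Under Randomization and blinding, allocation is "stratified by professionals and volunteers", so the one adjustment factor is the stratification factor. The same section gives the order of events: "After retrieval of written informed consent and baseline data, participants will be allocated to the intervention group or to the control group".

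Under Data collection, the T0 variables for the legal representatives are "age, gender, education status, activity status (professional or voluntary representative), time since appointment as legal representative and number of persons concerned". Data analysis gives them two uses. One is description: "Baseline parameters are described by frequency tables, means, standard deviations or quartiles". The other is a comparison of early dropouts with the study population.

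Table 1 lists the knowledge test at T1 and T3 only, so no baseline knowledge score exists.

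**The concern.** In a linear model for a continuous score, a baseline variable that predicts the score takes variance out of the error term and narrows the confidence interval for the arm difference. The usual best candidate, the same test at baseline, is not available here. Education status and age are the natural substitutes for a test on study quality, decision processes and probabilities of benefit and harm. Time since appointment and number of persons concerned are weaker candidates.

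All four are known before allocation, so adjusting for them cannot introduce bias from post-randomisation information. The plan already uses this device elsewhere: the person-level outcomes at T3 are adjusted for their T0 values. What is at stake is the width of the primary interval and some reserve of power, not the validity of the test.

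**Working it through.** **Inputs from the article (Sample size, Data analysis).** Difference 0.085; common SD 0.17; two-sided α of 5%; 90% power; 86 evaluable per group; 20% dropout; 216 in total. The planning statement is: "A mean difference of 0.085 between IG and CG can be detected by a power of 90% by the two-sided t-test".

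**Step 1: reproduce the plan's figure.**
- Normal approximation: n = 2(1.960 + 1.282)² × 0.17² / 0.085² = 84.1, rounded up to 85 per group.
- Exact noncentral t: power is 0.8999 at 85 per group and 0.9032 at 86, so 86 per group is right.
- Dropout: 86 / 0.8 = 107.5, rounded up to 108 per group, or 216 in total.

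The stated figures hold, and they hold without any covariate gain.

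**Step 2: precision of the planned analysis.** SE = 0.17 × √(2/86) = 0.0259. The 95% half-width is about 0.0512.

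**Step 3: precision with added covariates.** Let R² be the share of variance, left after arm and professional status, that the added variables explain. Take 0.17 as the SD before that reduction. Then residual SD = 0.17 × √(1 − R²), and SE = residual SD × √(2/86). Power is from the noncentral t with 2 × 86 − 8 = 164 degrees of freedom. The article gives no R², so the values below are assumptions.

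| Assumed added R² | SE | Change in SE | 95% half-width | Power for 0.085 | n per group for 90% |
|---|---|---|---|---|---|
| 0 | 0.0259 | 0% | 0.0512 | 90.3% | 86 |
| 0.05 | 0.0253 | −2.5% | 0.0499 | 91.7% | 81 |
| 0.10 | 0.0246 | −5.1% | 0.0486 | 93.0% | 77 |
| 0.20 | 0.0232 | −10.6% | 0.0458 | 95.4% | 69 |

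**Step 4: cost if the covariates are useless.** With R² = 0, going from the 170 degrees of freedom of the plain t-test to 164 moves power from 90.32% to 90.31%.

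**Step 5: sensitivity to the SD.** The pilot estimates rest on 15 datasets before and 12 after the course, so 0.17 is uncertain. If the SD were 0.20 (an assumption for illustration), power for 0.085 at 86 per group would be 79.1%. An added R² of 0.10 or 0.20 would bring it to 83.2% or 87.2%.

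**The case against.** The strongest reply is that nothing here is wrong. Randomisation is stratified by professional status, the analysis adjusts for professional status, and the sample size was set for an unadjusted t-test whose power it meets. That stands in full.

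The second reply is that prognostic value is nowhere shown. The article gives no correlation or R² for education, age, time since appointment or caseload. Time since appointment and caseload may overlap with professional status, which is already in the model. Nine of the 13 items concern probabilities of benefit and harm of three specific interventions, and the Background says few representatives have a healthcare qualification, so personal characteristics may predict little. This also stands, and it is why the range starts at zero.

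The third reply is that the practical effect is small. The pilot effect was 0.38, and at that size power is about 100% with or without covariates. The Sample size section itself says the planned number exceeds what is theoretically needed. For the significance test this is fair if the pilot effect is near the truth. The interval would still narrow if the covariates predict the score.

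A reader might also infer that the same precision is lost in the T1 logistic model and the T1–T3 mixed model. That does not follow:
- A logistic model has no residual variance to shrink. Adding prognostic covariates generally does not reduce the standard error of the log odds ratio, and it changes which conditional odds ratio is estimated.
- In the compound-symmetry model for T1 and T3, the arm-by-time contrast is essentially within person, so covariates fixed in time barely affect it.

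Nor does chance imbalance make the planned analysis invalid, since the confidence interval and type I error already allow for it.

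**Conclusion.** The point holds as an optional efficiency improvement to the primary linear model, not as an error. The article fixes a model with arm and professional status only and leaves other pre-allocation variables out of it. Those variables, chiefly education status and age, may predict the score.

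At 86 per group the gain lies between nothing and a 10.6% smaller standard error, with power for 0.085 between 90.3% and 95.4%. This rests on an assumed added R² of 0 to 0.20, on 0.17 as the SD before the added adjustment, and on 86 evaluable participants per group. The documents do not support saying that precision is definitely lost, that the trial is underpowered, or that the two-factor analysis is biased. The case for acting is the asymmetry: a possible gain of a few points of power against a loss of about 0.01 of a point.

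**What to change.** Before unblinding, state the primary linear model as arm + professional status + education status + age. Time since appointment and number of persons concerned at T0 may be added if their functional form is fixed in the same sentence. Name a simple imputation for missing baseline values, because the imputation rule in Data analysis covers outcomes only. Keep the arm-plus-professional-status model as a sensitivity analysis. Leave the logistic and T1–T3 models as they are on this ground.

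The cost is a sentence or two of text and a few degrees of freedom out of about 170. No new data are needed, and the sample size does not change.

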Antipsychotics	Documentation sheet; medical and nursing records	T3
PEG	Documentation sheet; medical and nursing records	T3

T1 = at the end of / up to 2 weeks after the intervention; T2 = 3 month follow-up; T3 = 6 month follow-up

Legal representatives in the IG will receive the test at the end of the education program. They may complete the test immediately or return it by mail in the following 2 weeks. Participants in the CG will receive the test by mail at the same time.

At T2 (the 3-month follow-up), the results of the first decisions regarding PEG, PR and AP for the persons concerned will be assessed (Table 1). Decisions may have been initiated by legal representatives themselves (e.g., consultation for medication review), by relatives (e.g., worries about agitation) or by health professionals (e.g., required consent for PEG or PR). We define a decision as every consideration about PEG, PR or AP, regardless of the result.

Participants receive a documentation sheet for each intervention at the beginning of follow-up to assess the starting point of the decision-making process, presence of the intervention before and after the decision, reason or trigger for decision-making and changes regarding the intervention. The sheets may be used for personal documentation only or may be sent back to the study center.

Participants will be contacted by phone to ask if they had made a decision regarding PEG, PR and/or AP. If they had made a decision, they will either be reminded to fill out and return the documentation or directly interviewed by telephone to fill out the sheet. The first decision of each intervention will be recorded and classified in one of the four following categories, whereby 0 = no presence and 1 = presence of PEG, FEM and AP:

Category I: 0 ➔ 0 (No PEG / FEM / AP ➔ decision ➔ no PEG / FEM / AP).

Category II: 0 ➔ 1 (No PEG / FEM / AP ➔ decision ➔ new PEG / FEM / AP).

Category III: 1 ➔ 1 (PEG / FEM / AP ➔ decision ➔ still PEG / FEM / AP).

Category IV: 1 ➔ 0 (PEG / FEM / AP ➔ decision ➔ no longer PEG / FEM / AP).

The date of the decision will be documented.

At T3 (the 6-month follow-up), the sustainable knowledge of legal representatives will be assessed using the same test as at T1.

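### Compound symmetry in the T1–T3 knowledge model forces equal variance at the two visits, so the standard error of a T3 arm difference is mis-sized if the variances differ; an unstructured 2×2 matrix removes this at almost no cost

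*Protocol article*

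**What the plan says.** The Outcomes section of the protocol article lists sustainable knowledge, measured six months after the intervention, as a secondary outcome. The Data collection section repeats that at T3 "the sustainable knowledge of legal representatives will be assessed using the same test as at T1".

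The Data analysis section states: "The sustainability of knowledge will be investigated at T3". It continues: "The time course of the knowledge between T1 and T3 will be analyzed by fitting a linear mixed model". The fixed effects are group, time (T1, T3), "interaction between intervention and time, professional status and interaction between intervention and professional status". On the within-person covariance it says that "random effects are included (covariance pattern model with covariance structure compound symmetry".

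No other analysis of T3 knowledge is described. The article does not say whether sustainability is tested by the arm difference at T3 or by the group-by-time term. Missing primary and secondary outcomes are to be imputed by simple methods.

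The only SD in the article is in the Sample size section: "A common standard deviation of σ = 0.17 can be assumed in IG and CG". It is a planning value for the T1 primary outcome and is not broken down by visit.

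**The concern.** Compound symmetry has two parameters, one variance and one covariance. With two visits, the variance at T3 is therefore not estimated from T3 data alone but averaged with the variance at T1. A T3 arm difference taken from the model then carries a standard error that is too small if scores are more spread out at T3 than at T1, and too large if they are less spread out.

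Some change in spread is conceivable. The score is a percentage correct on 13 items and so is bounded. T1 follows the course directly or within two weeks, while T3 comes six months later, when some participants will have retained more than others. At stake are the confidence interval and p-value for one listed secondary outcome.

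**Working it through.** **The plan's own figure.** The sample size rests on SD 0.17, difference 0.085, two-sided 5% and 90% power. An exact t-test calculation gives power 0.8999 at 85 per group and 0.9032 at 86, so 86 is right. Allowing for 20% dropout, 86/0.8 = 107.5, rounded up to 108 per group, or 216. This concerns T1 only; nothing comparable is stated for T3.

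**Inputs for the check.**
- n = 86 per group and a control SD of 0.17 at both visits, from the Sample size section. Holding the control SD constant is my assumption.
- Intervention-group SDs at T1 and T3: assumed, because none are given.
- Balanced data, as the planned imputation would produce. Professional status is left out of the formulas.

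**T3 arm difference.** Let v be the variance in each arm-by-visit cell.
- Correct SE = √(2·V3/n), where V3 is the mean of the two T3 variances.
- Compound-symmetry SE = √(2·V/n), where V is the mean of all four cell variances.
- Ratio = √(V/V3), which does not depend on n. Actual two-sided level = 2·[1 − Φ(1.96 × ratio)].

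The control group contributes 0.17² = 0.0289 at each visit.

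| Intervention SD, T1 → T3 | V | V3 | Compound-symmetry SE | Correct SE | Ratio | Actual level |
|---|---|---|---|---|---|---|
| 0.17 → 0.17 | 0.02890 | 0.02890 | 0.0259 | 0.0259 | 1.000 | 5.0% |
| 0.14 → 0.17 | 0.02658 | 0.02890 | 0.0249 | 0.0259 | 0.959 | 6.0% |
| 0.14 → 0.20 | 0.02935 | 0.03445 | 0.0261 | 0.0283 | 0.923 | 7.0% |
| 0.20 → 0.14 | 0.02935 | 0.02425 | 0.0261 | 0.0237 | 1.100 | 3.1% |

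For example, in the third row V = (0.0289 + 0.0289 + 0.0196 + 0.0400)/4 = 0.02935, V3 = (0.0289 + 0.0400)/2 = 0.03445, √(0.02935/0.03445) = 0.923 and 1.96 × 0.923 = 1.809.

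**Group-by-time contrast.** The correct variance is the sum over arms of (v1 + v3 − 2c), divided by n, where c is the T1–T3 covariance. Under compound symmetry it is 2·(2V − 2C)/n, where C is the mean of the two covariances. Since 4V is the sum of the four variances and 4C is twice the sum of the two covariances, the expressions are identical. For the 0.14 → 0.20 case at correlation 0.5, both equal 0.0605/86, an SE of 0.0265.

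**Simulation.** REML random-intercept fits were run 300 times per scenario with 86 per group, correlation 0.5 and the same SDs in both arms. An empirical SE from 300 runs carries an error of about 4%.
- SD 0.17 to 0.204: the T3 difference had model SE 0.0286 against empirical 0.0309; the change contrast had 0.0287 against 0.0290.
- SD 0.13 to 0.20 with 20% of T3 missing and not imputed: the T3 difference had 0.0274 against 0.0332; the change contrast had 0.0286 against 0.0299, within simulation error.

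**The case against.** The strongest reply is that the stated aim of the model is the time course from T1 to T3. The contrast that matches this aim is group by time, and its standard error is right under compound symmetry with balanced data. That stands, and it limits the point to the T3 arm difference. It does not remove the point. The article defines sustainable knowledge as knowledge at six months and offers no other analysis of it, and a group-by-time term cannot show whether the trained group still knows more at T3.

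A second reply is that nothing in the article shows that the spread changes. A reader might infer a ceiling at T1 from "The pilot study estimated a larger effect (0.38"), but the article gives no baseline mean. With four choices per item, chance is 25%, and 0.25 + 0.38 = 0.63 is not a ceiling. The Sample size section itself discounts that effect for small numbers and possible bias. This also stands: unequal variance is possible, not shown.

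A reader might also apply the change in spread to both arms, which gives larger errors. For 0.14 to 0.20 the ratio is √[((0.0196 + 0.0400)/2)/0.0400] = 0.863, an actual level of about 9.1%. The mechanism, however, concerns trained participants, and controls are offered the course only after their six-month data are in. The one-arm figures are the fairer illustration.

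Finally, a reader might take the sentence to combine a random intercept with a separate covariance pattern. A random intercept itself implies compound symmetry, so the bracket reads naturally as naming the same structure.

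**Conclusion.** The equal-variance constraint is real and explicitly stated. It matters for one contrast, the T3 arm difference, and only if the arm-averaged variance differs between T1 and T3. Under the one-arm assumptions above, a nominal 5% test would run at about 6% to 7% if intervention-group scores spread out by T3, and at about 3% if they narrow. The direction is unknown, and every visit-specific SD used is an assumption.

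A reader might infer that the model gives wrong standard errors whenever training changes the spread. The article does not support that. Pre-training knowledge is not in this model, the change contrast is unaffected with balanced data, and the primary T1 comparison uses a separate two-factor analysis of variance. The sample size is unaffected as well. The point is an improvement worth making to a secondary analysis, not a demonstrated error.

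**What to change.** In the Data analysis section, replace compound symmetry with an unstructured 2×2 within-person covariance (separate variances at T1 and T3 plus one covariance). Name the arm difference at T3, estimated from that model, as the sustainability contrast. The group-by-time term can stay as the description of change.

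The cost is one parameter, three in place of two, estimated from 172 to 216 participants. No additional data are needed. If the two variances turn out equal, the result is practically the same as under compound symmetry.
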